### Qualitative Exit Interviews

To qualitatively evaluate feasibility and acceptability, we will conduct brief exit interviews with a subset of study participants (n=20), purposively sampled to represent different ethnicities, religions, genders, and immigrant backgrounds. Additionally, we will conduct interviews with each PF at the end of the study. These interviews will be conducted by trained staff via Zoom.

### Statistical Analysis

We will conduct descriptive analysis to assess the acceptability, feasibility, and safety of Weyera. To evaluate the acceptability of the intervention, descriptive quantitative analyses of the intervention data will focus on tabulating and summarizing the results of the postsession satisfaction survey measures. To determine feasibility, we will monitor recruitment rates, effort required (eg, staff hours), number of screenings, and the proportion of eligible participants who agree to enroll. We will summarize rescheduled, canceled, and missed sessions to help estimate staffing needs and retention protocols for a future full trial. Additionally, we will compare the characteristics of participants lost to follow-up with those who remain to identify any systematic patterns that may affect the results. Safety will be assessed by tabulating and describing any adverse events during study participation.

Additionally, we will measure mental health outcomes, hypothesized moderators, and background (risk) factors to evaluate the feasibility of data collection (eg, time to complete surveys), as depicted in Table 1. To analyze changes over time, we will plot means and proportions from baseline to follow-ups. Exploratory hypotheses will be evaluated using linear mixed models, estimated via maximum likelihood, and fitted to provide all necessary information for analyses typical of a full randomized controlled trial [44]. We will also assess the feasibility of interaction analyses (for effect modification). As of March 2026, the study has enrolled 65 participants (33 in the intervention group, 32 in the control group) who have completed the baseline survey. We have not started data analysis.

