**Conclusions:**

The trial is poised to demonstrate that the Weyera intervention is feasible, acceptable, and safe among Ethiopian and Eritrean immigrant youth. This work will add to the knowledge of using group-level interventions facilitated by trained peer facilitators to enhance resilience and improve mental health in this population.

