## Methods

### Study Objective

The overall objective of this study is to develop and pilot test Weyera to assess feasibility, acceptability, and safety before conducting a fully powered trial. We aim to accomplish this through two specific objectives: (1) to develop Weyera, a culturally responsive mental health support intervention for Ethiopian and Eritrean emerging adults, in partnership with youth and community stakeholders; and (2) to conduct a pilot trial of Weyera and evaluate its feasibility, acceptability, and safety among emerging adults in Atlanta.

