### Ethical Considerations

The Institutional Review Board at Emory University has reviewed and approved all procedures outlined in this protocol (STUDY00008231 approved on August 25, 2024). The study is registered with ClinicalTrials.gov (NCT06960187). Our team works closely with a Licensed Master Social Worker, who is on-call during all sessions, to consult the PFs in case participants exhibit signs of a mental health crisis or distress. PFs are also trained in the correct referral methods in such situations. Informed consent will be obtained by the research team during the initial Zoom call before enrollment into the study. The team will explain the potential risks and adverse effects associated with participation, including potential discomfort or unpleasant experiences during group activities, as well as the possibility of confidentiality breaches. All participants are also provided with a list of affordable local mental health resources upon enrollment. Additionally, participants are encouraged to step away if they feel uncomfortable during a session. If any study participant reports feeling uncomfortable or unsafe during any session, the study team will work to address the issue as best as possible and offer the participant the option to withdraw from the study at any time. The study team will also track and report any adverse events to the Institutional Review Board. Participants will receive US $25 compensation for each session attended.

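### Acceptability, a primary aim, is drawn from session attendees' forms and from interviews not sampled on attendance, so people who stop coming are under-represented in both participant sources

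*Protocol article*

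**What the plan says.** The Study Objective section gives the purpose as "to assess feasibility, acceptability, and safety before conducting a fully powered trial", and the abstract's Methods put these three aims ahead of the exploratory outcomes.

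For acceptability, the Statistical Analysis section says that the quantitative analyses "will focus on tabulating and summarizing the results of the postsession satisfaction survey measures". The Participant Experience section has participants fill in an evaluation form for each weekly session and ties a US $25 payment to it. Ethical Considerations makes that payment conditional on attending the session.

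The second participant source is a set of 20 exit interviews, "purposively sampled to represent different ethnicities, religions, genders, and immigrant backgrounds". Attendance and withdrawal are not among the sampling dimensions. The Participant Experience section mentions the interviews, together with the 2-, 4- and 6-month survey links, as following completion of the program. The Data Collection section lists the same survey times without any such condition.

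On attrition, the Statistical Analysis section says "we will compare the characteristics of participants lost to follow-up with those who remain" and does not mention arm. The Limitation and Future Directions section says the wait-list group may drop out more.

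The abstract's Conclusions read: "The trial is poised to demonstrate that the Weyera intervention is feasible, acceptable, and safe". Expected Findings says much the same.

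**The concern.** A post-session form can only record the opinion of someone who was at the session. A participant who dislikes the program and stops coming gives no further rating, so the remaining forms describe a group selected partly by its own satisfaction. If leavers are less satisfied than stayers, the reported figure exceeds the value for everyone assigned, and the gap grows as attendance falls.

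The interviews could correct this, but not as they are specified. A sample spread over ethnicity, religion, gender and immigrant background can consist entirely of completers, and the Participant Experience wording points that way.

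At stake is what the pilot tells the designers of the full trial. A high satisfaction figure from those who stayed does not say whether the program suits the people who will be enrolled. The reasons for leaving, which are the most useful information for redesign, are what these two sources are least likely to capture.

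**Working it through.** The article gives no acceptability figure to reproduce. The sample size of 60 is justified descriptively, which is not in question here.

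**Inputs from the article.** Enrolled as of March 2026: 65, with 33 in the immediate group and 32 in the delayed group (Statistical Analysis). Both groups are offered the program, the delayed group after 2 months.

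**Assumed inputs.** The article gives no attendance or satisfaction rates. Those below are illustrations, and satisfaction is treated as yes or no.

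**Formulas.** Let N be the number assigned, a the number completing the form, and s the number of those who are satisfied.

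- Figure as planned: s/a
- Lower bound over all assigned (no non-responder satisfied): s/N
- Upper bound over all assigned (every non-responder satisfied): (s + N − a)/N
- Width of the range: (N − a)/N, the proportion without a form

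**One session, immediate group.** N = 33, a = 22, s = 20 (a and s assumed).

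- As planned: 20/22 = 91%
- Lower bound: 20/33 = 61%
- Upper bound: (20 + 11)/33 = 31/33 = 94%
- Width: 11/33 = 33 percentage points

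**Both arms, N = 65**, with about 90% of form completers satisfied:

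| Form completers (a) | Satisfied (s) | As planned, s/a | Lower, s/N | Upper, (s + N − a)/N |
|---|---|---|---|---|
| 58 | 52 | 90% | 52/65 = 80% | 59/65 = 91% |
| 52 | 47 | 90% | 47/65 = 72% | 60/65 = 92% |
| 46 | 41 | 89% | 41/65 = 63% | 60/65 = 92% |
| 32 | 29 | 91% | 29/65 = 45% | 62/65 = 95% |

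The planned figure stays near 90% in every row, while the lower bound falls from 80% to 45%. The figure by itself therefore cannot distinguish a program most people liked from one that nearly half left. It also lies close to the upper bound throughout, so reading it as the value for all assigned amounts to assuming that leavers were about as satisfied as stayers.

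**Interviews and follow-up, side by side.** Participant Experience links both the follow-up surveys and the interviews to finishing the program. Data Collection sets surveys at baseline and at 2, 4 and 6 months with no link to completion. Under the first reading, someone who leaves at week 3 receives neither a survey link nor an interview; under the second, the surveys still reach them. The text does not settle which applies.

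**The case against.** Several objections have force.

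- **Leavers are recorded.** The Data Collection section provides an attendance and engagement tracker. The Statistical Analysis section summarizes missed sessions and compares those lost to follow-up with those who remain. Low attendance would therefore be visible beside high satisfaction. This stands, and it rules out the inference that dropouts are invisible. These sources show who left, however, not what they thought of the program.
- **Other sources exist.** Interviews with every peer facilitator and post-session facilitator surveys add information. This also stands, but they are not the views of participants who left. The interview plan does not exclude leavers; it makes no provision for including them.
- **The direction of bias is assumed.** People miss sessions through illness or scheduling, and leavers may have been satisfied. This is correct, and is why a range is given and why an absence should not be counted as dissatisfaction.
- **This is a condensed article.** Criteria for proceeding to a full trial, exact limits and adverse-event procedures may sit in documents not shown. Their absence here is not a finding.

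A reader might go further and infer that safety is limited to attendees, since the social worker is someone "who is on-call during all sessions". The text does not support this: "Safety will be assessed by tabulating and describing any adverse events during study participation" covers both arms and the waiting period, and the on-call arrangement is crisis support, not a stated limit on how events are found. Nor is there a distorted comparison of harms between arms, because none is planned. Waiting controls are not unobserved either: they complete the baseline survey, fall under the Data Collection schedule, and later attend sessions and enter the satisfaction data.

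**Conclusion.** The concern holds in a limited form. Both participant sources on a primary aim favor people who keep attending, and the article states neither an all-assigned denominator for satisfaction nor a plan to hear from leavers. With an assumed one third of the immediate group giving no form, an attendee figure of 91% is compatible with anything from 61% to 94% of those assigned. The size depends entirely on attendance: the range is as wide as the proportion without a form, so it would be small if nearly everyone attends.

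Two smaller points go with it. The article expects higher dropout in the wait-list group but does not say attrition will be shown by arm; nor does it say the arms will be pooled. The Conclusions and Expected Findings also anticipate a favorable answer before analysis has begun. It would be too strong to read this as a positive verdict built into the trial. The data could turn out unfavorable, and Expected Findings also presents the trial as giving evidence on whether the approach works. The fault is one of wording that runs ahead of a descriptive analysis.

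**What to change.** 1. Within the existing 20 exit interviews, add attendance as a sampling dimension and reserve places for early leavers and low attenders in both arms. Reconcile the Participant Experience and Data Collection sections so that interviews and follow-up surveys do not depend on completing the program.
2. For each session and overall, report by arm the satisfaction among form completers beside the number and proportion of all assigned participants who attended and were satisfied, with lower and upper bounds for those who gave no form. Do not label every absence as dissatisfaction.
3. Report attrition by arm at each survey.
4. Reword the abstract's Conclusions and Expected Findings to say that the trial will describe feasibility, acceptability and safety, without anticipating the answer.

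Items 2 and 3 should need only the forms, attendance records and surveys already planned. They can be fixed now, since the article states that analysis has not started. Item 1 keeps the number of interviews, but data collection is expected to end in April 2026, so it can apply only to interviews not yet held. The costs are fewer interviews with completers, a few more table columns, and possibly a less favorable acceptability figure.

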6. Mental health issues in our community	Explore the different mental health issues that are common in the communities Talk about therapy and medication as treatments for mental health issues How to access psychotherapy when it’s needed	How to book a consultation with a therapist Practice questions to ask when establishing care	
7. Trauma	Discuss trauma, adverse childhood experiences How to make the communities more trauma-informed	Grounding activity (what to do in the moment) Safety plan (what to do in the future)	
8. Resilience and program reflection	Talk about resilience—how all these aspects come together to help build our ability to cope and emerge from difficult experiences Reflect on the last 8 weeks and then we say goodbye!	Personalized affirmation for another participant in the group	

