### Sample Size and Power

The goals of this study are to assess feasibility, acceptability, and safety. The proposed sample size of 60 participants was not derived based on estimating effect size estimates (which are often unreliable from small pilot studies [32-41]), but to provide a sufficiently large sample to obtain reasonable descriptive data and to pilot test our data collection procedures, intervention manual, and recruitment and retention methods, in anticipation of a future fully powered efficacy trial. The qualitative sample size is based on Kvale’s estimate that 15±5 individuals are typically sufficient to reach thematic saturation [42].

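### Safety is a stated goal, but it is assessed only by tabulating adverse events; worsening on the PHQ-9, GAD-7 and PTSD checklist is not part of the safety assessment

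*Protocol article*

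**What the plan says.** Sample Size and Power puts safety on a level with the other two aims: "The goals of this study are to assess feasibility, acceptability, and safety". The Conclusions of the Abstract and the Expected Findings section both anticipate showing that the program is safe.

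Statistical Analysis then says how safety will be judged: "Safety will be assessed by tabulating and describing any adverse events during study participation". No other safety measure is named. Ethical Considerations adds that adverse events are tracked and reported to the review board, and it describes a social worker on call during sessions. The participation risks it lists are "potential discomfort or unpleasant experiences during group activities" and breaches of confidentiality.

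The symptom scales (PHQ-9, GAD-7 and a 20-item PTSD checklist, all in Table 2) are scheduled at baseline and at 2, 4 and 6 months. Statistical Analysis introduces them with a different purpose: "we will measure mental health outcomes, hypothesized moderators, and background (risk) factors to evaluate the feasibility of data collection". Two further uses follow: "To analyze changes over time, we will plot means and proportions from baseline to follow-ups" and "Exploratory hypotheses will be evaluated using linear mixed models, estimated via maximum likelihood". The Abstract also says that possible effects on depression, anxiety and trauma will be explored. (The analysis section cites Table 1 for these measures; they are in Table 2.)

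**The concern.** Trained peers lead the groups through family relationships, pressure and fear of failure, race and identity, and, in module 7, trauma: "Discuss trauma, adverse childhood experiences How to make the communities more trauma-informed". Worsening of depression, anxiety or PTSD symptoms is a plausible harm of such content. Table 2 itself describes the PHQ-9 and the PTSD checklist as monitoring tools.

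Symptoms will also be common whatever the program does. The team's earlier survey, reported in the Introduction, found 49.2% above the depression threshold and 57.4% with at least mild anxiety, and the trial has no symptom criterion for entry. Against that background, a list of events is hard to interpret without a comparison.

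Most of the harm-detection channels described are tied to sessions, and waiting participants attend none. The symptom surveys are the one harm-relevant measure planned for everyone, yet they sit outside the safety assessment. At stake is the statement that the program is safe, which is meant to support a later powered trial.

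**Working it through.** The plan states no figure for safety (no rate, margin or power), so there is none to reproduce. The check is a reading of the text plus arithmetic on assumed rates.

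**1. Where each source of harm information goes**
- Adverse events: safety (Statistical Analysis).
- PHQ-9, GAD-7 and PTSD checklist: data-collection feasibility, plots of means and proportions, exploratory mixed models (Statistical Analysis).
- Post-session surveys: acceptability (Statistical Analysis).
- Exit interviews: feasibility and acceptability (Qualitative Exit Interviews).

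Only the first feeds the safety assessment.

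**2. Can the planned summaries hide individual worsening?** The rates and point changes here are assumed; 33 is the enrolled immediate arm.
- Mean: 8 people worsen by 5 points and 25 improve by 2. Change = (8 × 5 − 25 × 2)/33 = (40 − 50)/33 = −0.3.
- Mean, second case: 15% worsen by 5 and 85% improve by 2. Change = 0.15 × 5 − 0.85 × 2 = −0.95.
- Proportion above a threshold: start with 16 of 33 above it (48%). If 8 rise above and 8 fall below, the count is 16 − 8 + 8 = 16, so the plotted proportion does not move.

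In the first two cases the plot shows improvement, and in the third no change, while individuals deteriorate.

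**3. How much can an empty adverse-event table support?** With zero events the one-sided 95% upper limit is 1 − 0.05^(1/n).
- n = 33: 8.7%.
- n = 65 (all enrolled): 4.5%.

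These limits concern recorded events only. They say nothing about worsening that is not recorded as an event.

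**4. What precision would a deterioration table have?** Assume about 10% worsen while waiting and 25% in the program: 0.10 × 32 ≈ 3 and 0.25 × 33 ≈ 8.
- Difference = 8/33 − 3/32 = 24.2% − 9.4% = 14.9 points.
- SE = √(0.094 × 0.906/32 + 0.242 × 0.758/33) = 0.091.
- Wald 95% interval ≈ 14.9 ± 17.8, or about −3 to +33 points.
- Power of a two-sided 5% comparison at 30 per arm: 19% for 10% versus 20%, 49% for 10% versus 30%, 78% for 10% versus 40%.

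The table can describe and flag, but it cannot serve as a test.

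**5. Is there an untreated 2-month comparison?** The article gives two schedules.
- Data Collection lists baseline, 2, 4 and 6 months. If these run from enrollment, the delayed arm's 2-month survey falls at the end of its 2-month wait.
- Participant Experience places the 2-, 4- and 6-month surveys after program completion. The delayed arm's first follow-up would then come about 2 (wait) + 2 (8-week program) + 2 = 6 months after enrollment, with no unexposed survey except baseline.

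The comparison in step 4 exists only under the first reading, and only if the survey is completed before the delayed arm's first session.

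**The case against.** The strongest reply is that this is an article. The definition and grading of adverse events, and the layout of the safety tables, normally sit in the full protocol or analysis plan, which is not shown. That stands, and it rules out several stronger readings a reader might infer.

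- *The scales serve only data-collection feasibility.* Not so: plots over time and exploratory mixed models are also planned, so average worsening would be visible.
- *Harm would not count against the program.* The article does not define an adverse event, and worsening or observed distress could be recorded as one. The supportable wording is that it need not count.
- *Only spontaneous reports are captured.* Nothing says so. Staff respond to observed signs of distress, and there are post-session surveys of participants and facilitators and weekly debriefs. The article does not say whether these feed the adverse-event table.
- *Events will be pooled over waiting, program and later time.* The wording sets an inclusive scope; it does not fix a pooled table.
- *The program is trauma-focused.* One module of eight is on trauma, and its listed activities are grounding and a safety plan.
- *An untreated 2-month comparison is available at no extra cost.* The two schedules conflict, so this is unsettled.

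It is also fair to say that a deterioration table at this size would be descriptive only, like the safety approach already planned.

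What the reply does not remove is that the article does more than stay silent. It states how safety will be assessed, gives the symptom scales other uses, and anticipates a conclusion of safety.

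**Conclusion.** The point holds in limited form. As written, the safety conclusion rests on tabulated adverse events alone, and symptom data planned for every participant are not part of it. Deterioration that nobody records as an event could be left out, and means or net proportions can conceal it.

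The size cannot be estimated from the article, which gives no worsening or event rates. The 3-versus-8 example and the point changes are assumptions that show the mechanism, not predictions. The intervals treat participants as independent, although sessions run in groups of about eight. The gap is worth closing before analysis, but it does not invalidate the trial.

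**What to change.** Before analysis starts (the article says it has not), make these changes:

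1. State in the safety assessment whether worsening on the PHQ-9, GAD-7 and PTSD checklist counts as a safety outcome. Report, by randomised arm and for each scale, the number and proportion who worsen from baseline by a margin the study team fixes in advance, with confidence intervals and no hypothesis test.
2. Show adverse events by arm and by exposure period: waiting, during the program, and after it.
3. Reconcile the survey timing in Participant Experience with that in Data Collection. Use the 2-month survey as the untreated comparison only if the delayed arm is confirmed to have completed it before starting the program. If not, report worsening by arm and exposure period without claiming an untreated control.
4. Correct the reference to Table 1 in Statistical Analysis to Table 2.

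The cost is some analysis wording and one or two tables, from data already planned if the schedule is confirmed. The downsides are wide intervals with about 32 per arm, some chance signals across three scales, and a safety statement that may become less favourable.
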